## Abstract

**Background:**

The first thousand days post-conception are crucial for potential interventions to improve early child growth and development. Adequate nutrition during pregnancy plays a pivotal role in both maternal and child health. Recent studies indicate that the consumption of animal-source foods (ASF) such as eggs during childhood may have a positive effect on child growth and development. However, limited evidence exists for the impact of egg supplementation during pregnancy on maternal and child nutrition. The *Deux Oeufs* study aims to test the effect of a maternal nutritional intervention of two eggs per day during pregnancy on birth outcomes and infant growth.

**Methods:**

*Deux Oeufs* is a randomized controlled trial (RCT) and will aim to enroll and randomize 956 pregnant women from *Nyagatare* District in Rwanda into one of two study arms: a treatment group (T1) or a control group (T2). Women in the treatment arm will consume a supplement of two eggs per day starting from enrollment during the first trimester of pregnancy until childbirth. The study staff will directly observe the consumption of eggs daily. Women in the control arm will continue their usual diet. All enrolled participants will receive standard prenatal care, as outlined by the Government of Rwanda (GoR), a mobile phone, health insurance (if not already covered), and modest compensation for participation. All participants who are not already receiving Shisha Kibondo (a fortified flour supplement provided by GoR) as part of their standard care will receive the same amount (6 kg/month) from the study, regardless of treatment arm. The primary outcome is child length-for-age z-score (LAZ) at birth. Secondary outcomes include maternal health indicators (during and after pregnancy) and child growth and early development measures both in utero, during the second and third trimesters, after birth, and at 6 weeks and 6 months of age. Women will be enrolled on a rolling basis starting from May 2024.

**Discussion:**

*Deux Oeufs* is the first RCT to test the effects of directly observed daily maternal egg consumption during pregnancy on child nutrition outcomes. Findings from the study will provide evidence on the potential for prenatal ASF supplementation to improve child growth and development and consequently inform policy decisions.

**Trial registration:**

ClinicalTrials.gov NCT06405360. Registered on May 03, 2024.

## Background and rationale {6a}

Inadequate and less diverse diets during critical life stages, including pregnancy, lactation, and infancy, are major contributors to childhood malnutrition, particularly in low- and middle-income countries (LMICs) [29]. The first thousand days post-conception are recognized as a critical period of potential intervention to improve early childhood development and reduce stunting [9, 28, 45]. Maternal nutritional status has been shown to directly affect the occurrence of child stunting, as well as indirectly affect stunting through other factors [44]. Research has revealed that intrauterine growth faltering is a more significant problem than previously realized [11] with approximately 20% of stunting occurring in utero in LMICs [6, 41]. Empirical studies consistently show that fetal growth restriction often originates in utero and is intrinsically linked to maternal nutrition [13, 32]. In addition to its role in child development, maternal nutrition is a key determinant of overall maternal and neonatal health, influencing pregnancy outcomes, fetal development, and birth outcomes [27]. This underscores the pivotal role of maternal diet in improving both maternal and fetal health outcomes.

The increase in nutritional demands during pregnancy and lactation is well established. Pregnant women have higher requirements for certain micronutrients such as iron, magnesium, and zinc [39]. Evidence indicates that poor maternal nutrition is responsible for around 800,000 neonatal deaths each year [4, 34]. Maternal anemia and calcium deficiency are key factors linking maternal nutrition to maternal mortality and adverse pregnancy outcomes. In LMICs, maternal anemia is estimated to contribute up to 12% to low birth weight cases, 19% to preterm birth cases, and 18% to perinatal mortality [42].

Consequent to these, there observations have been significant emphasis on improving nutrition during the critical first 1000 days from conception to 2 years of life. However, many of these efforts have focused on the fortification of foods, including US Title II food aid products. Blended flours, such as corn soy blends (CSB), have been a staple of development efforts and food aid programs, and the increased understanding of the critical role of animal proteins and micronutrients has led to the fortification of these with essential vitamins and minerals and milk powder, often referred to as CSB+ and CSB++ or super cereal, respectively [50]. These fortified products are used widely to try to address the nutritional needs of both women and children [24].

In LMICs, typical diets are less diverse and often lack animal source foods (ASF), which are a rich source of bioavailable macro and micronutrients. This deficit is often because of barriers specific to LMICs (e.g., cost, poor supply chains, food insecurity, cultural norms) [1, 31]. Current food formulations (e.g., CSB+ , supercereals) are designed to enhance nutritional density and bioavailability. Notably, these nutritional attributes are naturally present in most ASF. The nutritional value of ASF has been highlighted as an important dietary tool in efforts to reduce child malnutrition due to high nutrient density and bioavailability of macronutrients [36], as well as essential micronutrients (vitamin B12, iron, choline, zinc, and iodine), which may be suboptimal in vegetarian diets [31]. Adequate amino acid supply is also important, especially during growth and development. In a meta-analysis by Pimpin et al. [40], both maternal and infant supplementation of animal protein was found to increase birthweight and young children’s weight. Given these nutritional advantages of ASF when compared to plant-based diets, there is an increasing dialogue around efforts to increase ASF in the diet, particularly in smallholder farming communities in LMICs [37], where dietary diversity is typically low and nutritional outcomes are poor [1, 10].

Among ASF, eggs are an excellent source of protein, essential fatty acids, and vitamins A and B12, as well as choline and docosahexaenoic acid (DHA), nutrients associated with child growth and cognitive development [21, 26]. Like other ASF across LMICs, eggs are rarely consumed among populations of women of reproductive age in sub-Saharan Africa, particularly in rural areas where rates of malnutrition are high, despite the relative affordability and availability of eggs compared to other ASF [1, 26].

Studies that examined eggs as a dietary tool to reduce malnutrition have focused on child egg consumption (at 6 months of age or later) or as part of a comprehensive package combined with other supplements [48] with little research exploring exclusively the impact of eggs among pregnant women as a mechanism to improve both maternal and child health outcomes. Consumption of eggs by infants and young children as a complementary food has been found to improve nutritional outcomes [22, 25, 30, 35] and early child development [14] in LMICs. Importantly, however, other studies have found that initial positive results in child growth outcomes following egg consumption were not sustained [20], and others still have found no impact [43, 47]. Another study by Pasqualino et al. [38] found no significant effect of egg supplementation in children (6–12 months) on length for age (LAZ) but did find a significant effect on weight.

Given the alignment of nutrient demand during pregnancy and the composition and bioavailability of nutrients in ASF, consumption of ASF during pregnancy has the potential to improve fetal growth in regions where malnutrition is prevalent. Further, because eggs prepared as hard boiled are safe and do not increase the risk of exposure to pathogens [15], and their nutrient profile indicates a potential to improve brain development, consumption of eggs during pregnancy has little to no risk [49] and offers other potential benefits to maternal and child development. Against this background and considering the existing lack of evidence, this randomized control trial (RCT) will address an existing gap in the literature surrounding the potential effect of maternal consumption of eggs on in-utero growth and brain development.

## Hypotheses and objectives {7}

The study hypothesizes that women who consume two eggs a day will have children whose LAZ at birth is significantly higher than LAZ among those born to women who consume a typical diet. The typical diet in Rwanda often includes fortified blended flour (FBF), a mixture of corn and soy with added vitamins and minerals, which is commonly provided by the government through various nutrition programs for children, undernourished pregnant women, mothers, and other vulnerable groups. FBF is often shared within the family. Therefore, all pregnant women in the study will receive CSB++ (if not already receiving from the government), and the comparison of the effects of eggs will be over a diet that consumes CSB+. The main objective of the study is to determine whether maternal egg consumption during pregnancy improves a child’s growth, which will be measured at birth, 6 weeks, and 6 months of age. The trial also aims to answer additional research questions related to maternal and child health, including the following:

*Maternal outcomes*
Does maternal egg consumption lead to improved maternal health indicators during pregnancy (including weight gain, blood pressure, anemia, and body mass index (BMI)) when compared to a typical diet?Do women who consume eggs during pregnancy experience reduced levels of anemia following birth compared to those who consume a typical diet?Does maternal egg consumption lead to improved prenatal and postpartum mental health of mothers, when compared to typical diet?

*Child outcomes*
Does maternal egg consumption lead to improved birth outcomes when compared to birth outcomes of mothers who consume a typical diet (birth outcomes will include miscarriage, stillbirth, preterm births, low-birth weight, small-for-gestational age)?Does any observed effect of maternal egg consumption on birth outcomes (compared to typical diet) differ by child sex (male/female)?Does maternal egg consumption improve other child growth outcomes (including stunting, wasting, and underweight) at 6 months of age compared to a typical diet?Does maternal egg consumption lead to improved levels of micronutrients (iron, vitamin B12, vitamin A) in children at 6 months of age compared to a typical diet?Does maternal egg consumption lead to improved neurodevelopment in utero (as indicated by ultrasound-based measures) or during the first 6 months of life (head circumference, Hammersmith Neonatal Neurological Exam (HNNE), and Caregivers-Reported Early Development Instrument (CREDI) scores compared to typical diet?

## Trial design {8}

The study is a randomized controlled trial (RCT) with parallel 1:1 assignment of participants to two study arms: (T1) two eggs per day (intervention) or (T2) typical diet (control). Block randomization will be stratified by gestational age group (09 < 11 weeks and 12 < 14 weeks). Women in the intervention arm will be asked to consume two eggs per day under the direct observation of study staff at a community health worker (CHW) home. Participants in the control arm will be asked to consume their typical diet, including CSB+. All participants will continue to receive standard care for pregnant women (antenatal care and institutionalized births among others), as outlined by the GoR. In addition, the study will provide a mobile phone, family health insurance (if not already covered), and modest compensation for participation. The amount of compensation was determined based on formative research and approved by the Rwandan National Ethics Committee (RNEC). The compensation for each engagement at the clinic (first, second, and third trimester visits, birth and two postpartum visits, at 6 weeks and 6 months of child age) was decided to be 3000 RWF. They will also be provided with transportation reimbursement for the study visits that occur at the health centers. All participants not receiving Shisha Kibondo (government brand for CSB++) from the GoR as part of their standard prenatal care will receive the same amount (6 kg/month) from the study. Figure 1 illustrates the study recruitment flow and treatment allocation.

**Fig. 1 Fig1:**
[figure not shown]
Study design of the *Deux Oeufs* randomized controlled trial

## Methods: participants, interventions, and outcomes

### Study setting {9}

The study will take place in *Nyagatare* District in the Eastern Province of Rwanda. *Nyagatare* District was selected because it (1) has a relatively high rate of stunting among children under 5 (30%) [33], (2) is within the USAID Feed the Future Zone of Influence, and (3) is not a district or region with the highest rates of malnutrition, where extensive and evolving government and nongovernmental nutritional interventions would challenge operational activities and the interpretability of the study’s findings. Pregnant women living in the catchment areas of *Ndama* Health Center in *Karangazi* sector will be the targeted population. *Ndama* Health Center was purposively selected as the study site because it serves a primarily rural population, and the reported historical number of births within the catchment area will provide a sufficient number of births for the study to meet enrollment targets. The selection of the study site was based on formative field work conducted in collaboration with the University of Rwanda and World Vision Rwanda from July through September 2023 and in concert with local, district, and national health officials.

### Eligibility criteria {10}

All pregnant women will be considered for enrollment, as per the eligibility criteria below.

#### Inclusion criteria

Lives in the study area (catchment area of *Ndama* Health Center)Ultrasound confirmed viable intrauterine pregnancyAged between 18 and 44 yearsUltrasound confirmed gestational age of 9 up to 13 weeks + 6 daysAgrees to participate and provides informed consent

#### Exclusion criteria

Intention to move outside the study area in the next 12 monthsIntention to deliver at a location outside of the Eastern provinceAny known adverse reaction to eating eggs or porridge ingredientsAny condition that could affect the ability to comply with the study requirements or understand the informed consent processParticipation in other clinical trials (to avoid the burden and potential interactions between interventions)Inability or unwillingness to comply with the study requirements, such as attending regular follow-up visits or adhering to prescribed nutritional supplementation

### Who will take informed consent? {26a}

The Rwanda National Ethics Committee (RNEC) and the Institutional Review Board (IRB) of the University of Florida approved the *Deux Oeufs* study. The study will fully comply with the code of ethics regarding participant enrollment, study assessment, and data protection. Trained World Vision study staff will administer an initial informed consent for screening, before performing a verbal eligibility assessment and conducting an ultrasound screening. When a study subject is screened for enrollment and is deemed eligible, she will be offered enrollment and engaged in a full informed consent process.

During the informed consent process, a study team member will communicate the study’s purpose, the assessments involved, the study process, and the potential benefits and risks involved to the participants in nontechnical language. Participants will have ample time to consider the study’s implications before deciding whether to enroll. Those who choose to participate must sign and date an informed consent form. In case of illiteracy, the study staff will ask for a thumbprint. Enrolled participants may withdraw from the study at any point in time. The original and signed informed consent forms will be retained with the participants’ records, and the participant will be provided with a copy of the signed consent form, as well as an information sheet, per RNEC requirements.

If any changes or amendments to the approved protocol directly affect a participant’s decision to continue in the study, the informed consent form will be amended accordingly. Participants will be required to re-sign the revised informed consent form after the same has been approved by the ethical committees of RNEC and the IRB at the University of Florida.

### Additional consent provision for collection and use of participant data and biological specimens {26b}

On the informed consent form, the research team will also seek participants’ consent to provide hair and blood samples, and for the study team to share the relevant data with regulatory authorities and IRB, where appropriate. Hair samples will be collected from mothers to assess cortisol levels, a hormone indicative of stress.

## Interventions

### Explanation for the choice of comparators {6b}

The intervention group will receive a daily supplement of two eggs (with consumption directly observed) from enrollment in the first trimester through childbirth. Both the intervention and control groups will receive standard information, education, and communication (IEC) about healthy diets and appropriate care during pregnancy. Participants will not be restricted from adding eggs or any other food to their diet.

All enrolled participants will receive the Government of Rwanda’s (GoR) up-to-date standard care for pregnant women, a mobile phone, health insurance (if not already covered), and modest compensation for traveling to a community health worker’s (CHW) home daily for study engagement. Additionally, any pregnant woman not already receiving the government-provided fortified corn-soy blend (CSB++ or *Shisha Kibondo*) will receive an equivalent amount (6 kg) from the study.

In order to uphold ethical considerations and account for potential spillover effects of the intervention, the study design does not include a true control group. The control group will receive the same level of care, information, education, and communication (IEC), and equal amount of CSB+; only egg supplementation will be different between the two groups. This design allows for a clear comparison of the effects of egg supplementation on pregnancy and child growth outcomes, beyond the benefits of a typical diet that includes CSB+ .

### Intervention description {11a}

All women enrolled in the study will be asked to visit a designated village-based consumption site (CHW’s home) daily. Sites must be within a 20-min walk from women’s homes. When a CHW house is not within a 20-min walk, additional sites (such as the home of a World Vision volunteer) will be identified close to the participant’s house. Study staff will prepare and transport hard-boiled eggs daily to CHWs’ houses (or designated consumption site), where CHWs will distribute eggs to the women in the intervention group every day. Study staff will observe and record consumption (no consumption, partial, or complete). The study staff will also ask about 24-h recall of quantity and consistency of CSB+ consumption and any adverse reaction or allergy to eating eggs. Women in the treatment arm and the control arm will both receive IEC communication. All women (treatment and control) will be compensated for their daily travel to the CHW’s house. The daily compensation of 500 RWF per day will be paid on a weekly basis if women attend at least 6 days in a week. However, in cases of excused absence, they will receive daily compensation for those days.

Participants in both the intervention and control groups will receive guidance to maintain their usual diets outside of the study intervention. No dietary restrictions will be imposed.

### Criteria for discontinuing or modifying allocated interventions {11b}

The intervention will be discontinued in cases of formal withdrawal, loss of follow-up, severe illness preventing study participation, and adverse events. If there is a loss of pregnancy, the woman in the egg group will continue to receive eggs for 30 days after miscarriage or fetal death if she wishes to. However, no daily cash compensation will be provided after the loss of pregnancy. Otherwise, the intervention (egg consumption) will end at childbirth.

### Strategies to improve adherence to interventions {11c}

Adherence to the intervention will be monitored throughout the study to ensure high uptake, with the goal of 100% adherence (daily observed consumption of 2 eggs per day, 7 days a week). Although 100% adherence is desired, the study team recognizes that the woman may not be present on certain days due to travel outside of the study area, work or family obligations, sickness, or other reasons. The woman also has the option of refusing the food on any given day. The study team will seek to document planned absences to anticipate the resumption of the nutritional supplement upon the woman’s return. To improve adherence, the women will also receive a small compensation for their daily visits to CHW houses (500 RWF per day) if they come at least 6 out of 7 days. However, in case of planned and excused absence, women will receive daily compensation for those days. The daily compensation amount was pilot tested in January and February 2024 to ensure that the payment was both motivational and effective. The compensation amount was then approved by ethical authorities (both Rwanda and UF) to be non-coercive. When a participant fails to present to the study team to receive her assigned supplement without prior notification of absence or explanation, a team member will attempt a visit to the village or study household later in the day to ensure adherence. Cell phones are provided by the study to optimize communication between the study team and all participating women. The food delivery staff who provide the eggs will attempt to reach women by telephone if they do not attend as expected, encouraging them to come to the CHW home, even later than designated. At the end of the day, however, if a participant has not come to the CHW home to receive the eggs, the staff may travel to her home to try to deliver and observe egg consumption. This will occur any day that the woman does not attend at the CHW home for egg consumption during the designated window but is considered a secondary option given the complexity around food sharing that may occur with the provision of eggs directly at homes.

If a participant is hospitalized and remains within the district of *Nyagatare*, the study team will deliver eggs to the facility, with the permission of health facility staff. Additionally, if the participant misses food supplement due to absence, refusal, or another reason but has not formally withdrawn from the study, the study team will attempt to contact the mother by phone or through CHW outreach every 2–4 days for up to 1 month to encourage re-engagement. If the participant re-engages with the study team, all intervention and data collection will be reinstated. Any barriers to participation identified during the study will be considered and addressed as much as possible by the research team.

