### Participant timeline {13}

Women will be recruited during the first trimester of pregnancy and will be asked to plan to remain in the study until the child is 6 months of age. Women will engage in study visits at the health center during the first (enrollment), second, and third trimesters of pregnancy. Additional follow-ups will be conducted at the time of birth (within 72 h) and when the child is 6 weeks and 6 months of age at the health facility. In addition, after enrollment, all participants will be asked to come to the CHW house every day to receive IEC messaging and eggs (intervention group only). Table 2 details participants’ timeline and assessments for the study.

**Table 2 Tab2:** Timeline of enrollment, intervention, and data collection from *Deux Oeufs* participants

	**During pregnancy**			**Birth**	**Post-birth follow-up**	
**Timepoint**	**GA (9– < 14 weeks)**	**GA (20–26 weeks)**	**GA (30–34 weeks)**	**Within 72 h**	**6 weeks**	**6 months**

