## Data collection and management

### Plans for assessment and collection of outcomes {18a}

At enrollment, an ultrasound screening will be conducted to determine eligibility, followed by a baseline survey on demographic and background characteristics of the household. Questions in the survey will include pregnancy and medical history, maternal behavior towards risk factors (e.g., malaria), physical activity, dietary diversity using the Dietary Quality Questionnaire (DQQ) (Global Diet Quality Project), household food security using the Household Food Insecurity Access Scale (HFIAS) [8], and water and sanitation practices. Women’s anthropometric measurements will be taken using Seca scales, including height (Seca 213 portable measuring rod), weight (Seca 874), and mid-upper arm circumference (MUAC). Blood samples and hair samples will also be collected at baseline.

During two additional clinical visits in the second (20–26 weeks) and third trimester (30–34 weeks), anthropometric measurements (height, weight, MUAC) from all women will be taken, as well as blood and hair samples. Ultrasound measurements will also be taken to assess fetal growth measures that include biparietal diameter, head circumference, abdominal circumference, and femur length. Information on medical conditions since the last visit, depression screening using the Edinburgh Postnatal Depression Scale (EPDS), physical activity, breastfeeding intention, consumption and preparation recall of CSB+, and maternal diet (DQQ) will be collected using a short survey during these visits.

At birth, anthropometric measurements of all neonates will be assessed twice within 72 h after birth, with the first 24 h as the target window. A third measurement will be taken in case of discrepancies between the first two measurements. For recumbent length, a third measurement will be taken if the difference between the first two measurements is more than 0.7 cm. A third weight measurement will be taken in case the difference in the weight in the first two measurements is more than 10 g. Length measurements will be taken using length board S0114540 set3, and weight will be measured using Seca 334 scale.

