### Adverse event (AE) reporting and harms {22}

Any adverse event, including a clinically significant abnormal laboratory finding, symptom, or disease temporally associated with the study, will be monitored and reported in detail in the participant’s records. AEs will be coded following MedDRA terminology to ensure consistent classification, analysis, and reporting. In trial publications, we plan to report all serious adverse events (SAEs) as well as any AEs deemed related to the intervention. The PI will evaluate and follow up with all AEs and inform regulatory bodies as appropriate (RNEC and UF-IRB) of measures that will be executed accordingly.

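### Follow-up of missed days and of pregnancy losses is written around egg delivery, so ascertainment of SAEs and losses is open to bias toward higher counts in the egg arm

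*Protocol article*

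**What the plan says.** Routine daily contact is the same in both arms. Intervention description {11a}: "All women enrolled in the study will be asked to visit a designated village-based consumption site (CHW’s home) daily". Participant timeline {13} repeats it: "after enrollment, all participants will be asked to come to the CHW house every day to receive IEC messaging and eggs (intervention group only"). Payment also covers both arms: "All women (treatment and control) will be compensated for their daily travel to the CHW’s house". Excused absences are paid, and every participant has a study phone.

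The response to a missed day is described differently. In Strategies to improve adherence {11c}, same-day follow-up starts when a woman does not come for her assigned supplement. The staff who bring the eggs make the calls, and "if a participant has not come to the CHW home to receive the eggs, the staff may travel to her home to try to deliver". For a woman in hospital within the district, "the study team will deliver eggs to the facility, with the permission of health facility staff". Contacts every 2–4 days for up to a month follow a missed food supplement; no arm is named.

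After a pregnancy loss, Criteria for discontinuing {11b} ends daily compensation for all, while "the woman in the egg group will continue to receive eggs for 30 days after miscarriage or fetal death if she wishes to". The adverse-reaction question at the daily visit ({11a}) asks about eating eggs.

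On reporting, Adverse event reporting and harms {22} covers any adverse event without distinction by arm and adds: "In trial publications, we plan to report all serious adverse events (SAEs) as well as any AEs deemed related to the intervention". At the 20–26 and 30–34 week visits, {18a} collects this from all women: "Information on medical conditions since the last visit".

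**The concern.** A woman who is admitted to hospital or loses her pregnancy will usually miss her daily visit. How the team follows up that absence affects whether and when it learns of the event. If absences are pursued in one arm and not in the other, the arm with more tracing will record more events at the same true risk.

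Three uses of the data are exposed. All SAEs are to be published ({22}), and readers will compare the counts by arm. Safety is part of the review at about 100 births ({21b}). Miscarriage and stillbirth are among the birth outcomes to be compared between arms (Hypotheses and objectives {7}). A spurious excess with eggs would be a false safety signal, and a genuine excess would be hard to interpret because unequal tracing could explain it. The extra contacts are also made by intervention-delivery staff, who are not blinded ({17b}).

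**Working it through.** **1. Contacts compared by arm**

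| Contact | Egg arm | Control arm |
|---|---|---|
| Daily attendance, 500 RWF per day, paid excused absence ({11a}, {11c}) | yes | yes |
| Study phone ({11c}) | yes | yes |
| Visits at 20–26 weeks, 30–34 weeks, birth, 6 weeks, 6 months ({13}) | yes | yes |
| Same-day call and home visit after a missed day ({11c}) | yes | not stated; trigger and purpose are the eggs |
| Contact while in hospital ({11c}) | yes, by egg delivery | not stated |
| Re-contact every 2–4 days for up to 1 month ({11c}) | yes | unclear; trigger is a missed food supplement |
| Contact for 30 days after a loss ({11b}) | optional, through eggs | not stated; daily pay has stopped |
| Daily adverse-reaction question ({11a}) | about eggs | no arm-neutral question stated |

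**2. Which of the unequal contacts can reveal a new event?**

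- Egg delivery to a hospital requires that the admission is already known, so it does not detect the admission. It can reveal what happens later in the stay.
- The 30 days of eggs start once the loss is known, so they do not detect the loss. They can reveal complications or admissions in the following month.
- Same-day calls, home visits and the 2–4 day re-contacts can detect a first event in an absent woman.

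**3. Where the arms can differ**

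A control woman who attends, or who returns after an absence, is seen daily and has a paid reason to explain the absence. Two situations remain: a control who stops attending and is not traced, and the month after a loss, when a control has neither eggs nor daily pay to bring her back.

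**4. Size**

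The plan states no SAE rate and no detection probability, so there is no figure to reproduce. With equal true risk in both arms,

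apparent ratio = (detection in egg arm) / (detection in control arm).

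Assume full detection in the egg arm, a true risk of 10%, and 478 women per arm ({14}), so 478 × 0.10 = 47.8 true events per arm:

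| Assumed control detection | Apparent ratio | Excess events in egg arm |
|---|---|---|
| 100% | 1.00 | 0 |
| 95% | 1/0.95 = 1.05 | 47.8 × 0.05 = 2.4 |
| 90% | 1/0.90 = 1.11 | 47.8 × 0.10 = 4.8 |
| 80% | 1/0.80 = 1.25 | 47.8 × 0.20 = 9.6 |
| 70% | 1/0.70 = 1.43 | 47.8 × 0.30 = 14.3 |

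Let f be the share of control events that fall in the two situations of step 3, and d the detection there. If all other control events are detected, overall control detection is 1 − f(1 − d). The 95% row needs f(1 − d) = 0.05. The 70% row needs 0.30, meaning that 30% of all control events both fall in those situations and are missed. The documents support no value for f or d.

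**The case against.** The strongest reply is that controls are not out of sight. They are asked to attend every day, are paid for attendance and for excused absence, and carry study phones. CHWs keep a roster of village pregnancies (Recruitment {15}), and all women have scheduled ultrasounds and a birth visit. A control who is admitted or loses her pregnancy becomes a visible absentee the next day. The AE rule in {22} makes no distinction by arm. The re-contact passage names no arm and could cover both. The article is condensed, and detailed AE procedures may sit in the full protocol. No between-arm SAE test is stated, and {21b} says the interim review is not chiefly formal testing.

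Most of this stands, and it rules out a stronger reading that a reader might infer: that control events come to light mainly at the next scheduled visit, up to 26 − 9 = 17 weeks after enrollment, so that the SAE comparison is biased and a large share of SAEs is affected. That 17-week gap ignores the daily contact, and the documents give no basis for the share affected.

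The reply does not remove the narrower point. Daily attendance makes an absence visible in both arms, but the article describes a response only where a supplement has been missed. That is a procedure the article itself sets out, as is the post-loss contact, which is expressly limited to the egg group. Ambiguity about whether re-contacts cover controls is itself something to settle.

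**Conclusion.** Followed as written, the plan gives unequal tracing of absentees and unequal contact after a pregnancy loss, in a trial where participants and delivery staff know the allocation. Ascertainment of SAEs and losses is therefore open to bias toward higher counts in the egg arm. The exposure is confined mainly to control women who stop attending and to the month after a loss.

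Bias is possible but not established. Its size cannot be obtained from the documents, and it is zero if detection is equal, which daily contact in both arms makes plausible for women who keep attending. The ratios of 1.05 to 1.43 only restate assumed control detection of 95% to 70% and are not estimates. The primary outcome, birth LAZ, is not at issue here. The point is worth correcting because the remedy is cheap and events missed in untraced controls may not be recoverable later.

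**What to change.** 1. State in {11c} that absence calls, home visits and the 2–4 day re-contacts are triggered by non-attendance at the daily site in both arms.
2. At the daily contact and at every tracing contact, ask the same arm-neutral question on SAEs and pregnancy status in both arms, alongside the existing egg question.
3. Make one status contact about 30 days after a pregnancy loss in both arms. This is data collection only and leaves the egg offer in {11b} untouched.
4. Add a source-of-report field to the SAE form. Keep all SAEs in the main by-arm table and add a supportive tabulation by source. No known event should be removed: limiting the comparison to sources judged common to both arms would take genuine egg-arm events out of the safety table.

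The cost is an amendment of a few sentences, one form field, and some extra calls and occasional visits to absent controls by existing staff, using phones the women already have. Enrollment is paused (Trial status), which is a convenient time to amend. For women already followed, the by-source tabulation is informative only as far as the source can be recovered from existing records.
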